**Research Protocol**

The methodology for this project consists of four main stages:

1. Conducting a literature review to adapt an existing value framework.
2. Recruiting relevant stakeholders for input and feedback.
3. Adapting the framework based on stakeholder contributions.
4. Performing a statistical analysis of the collected data.

Additionally, the protocol includes a **Data Management** section, which outlines the procedures for handling and protecting data throughout the project.

**Process diagram**

**Stage 1: Literature Review and Initial Value Criteria and Value Sub-criteria Identification**

- The **Diagnostic Test Value Framework for Latin America** had previously identified 20 existing value frameworks, which were used as a foundation for the updates and changes made in the current review.
- A **systematic review (SR)** was conducted to identify value criteria and value sub-criteria that could potentially modify and adapt the existing value framework. The SR included a comprehensive search of both grey literature and primary research on relevant frameworks.
- The identified value criteria and sub-criteria were **mapped onto the existing framework**, ensuring that it accounted for the differential aspects of NGS-CGP (Next-Generation Sequencing-Comparative Genomic Profiling) technology.
- The **outcome** of this stage was a set of initial value criteria and value sub-criteria that served as the basis for the initial round of stakeholder engagement.
- The systematic review conducted in the first stage of the project was not registered, so no registration number is available. However, it was rigorously reported in accordance with the PRISMA checklist.

**Stage 2: Stakeholder Recruitment**

Two groups will be formed: a **steering committee (SC)** and a wider **collaborative stakeholder group**. Both the steering committee and the collaborative stakeholder group will be invited to participate in the framework adaptation activities described in Stage 3 through formal invitation letters.

Participants in both the steering committee and the collaborative stakeholder group will be identified by researchers through established professional networks. These networks included prominent organizations such as the ADVANCE HTA consortium, the IMPACT HTA consortium, WHO Europe Collaborating Centres, health insurance and payer organizations, HTA agencies, regulatory bodies, professional societies (e.g., ESMO), and patient advocacy groups, among others.

- The **steering committee** will established to oversee the research process and provide high-level guidance. As stated in the invitation to prospective members, the SC was tasked with advising on project methodology, overseeing IECS-LSE activities, and contributing to stakeholder group discussions. The SC members' expertise in value assessment and funding decisions for health technologies was considered essential for ensuring the research's validity and long-term sustainability.

Steering committee members will be invited via a formal letter and were expected to:

- - Participate in **four 60–90-minute meetings** over 12 to 18 months, including a kick-off meeting and one meeting at the end of each six-month research phase.
  - Advise on **project methodology and approach**.
  - **Review and approve** project deliverables.
  - Participate in **two or three rounds of stakeholder group preference elicitation** and consensus generation for adapting the VAF (Value Assessment Framework).

**Steering Committee Members:**

- [name] – London School of Economics
- [name] – Institute for Clinical Effectiveness and Health Policy
- [name] (Global Leader, Market Access, Roche, representing PCC)
- [name] – Patient advocacy
- [name] – Translational Cancer Genomics / Queen´s University Belfast
- [name] - Professor of Health Economics / University of York
- [name] - Italian Cancer Society
- [name] - Health Technology Assessment / Hospital Clinic Barcelona
- [name] - Institute of Pathology, University Hospital Heidelberg, Germany
- The **collaborative stakeholder group** will be formed by a minimum of 30 participants from European countries (focusing on the EU5 countries, as well as Sweden, the Netherlands, Austria, and Belgium). Participants will be divided into six subgroups based on their roles within the healthcare system. Similar numbers of participants will be recruited from each group to ensure balanced representation. All participants were required to have worked or be currently working in one of the study countries and represent one of the following categories:
  - Patient advocacy /civil society (e.g., ECPC-European Cancer Patient Coalition, Patvocates Research)
  - Decision-makers (e.g., MoH, EU, Procurement, HTAs, Hospital decision-makers)
  - HTA environment/ Regulators (e.g., EMA or notified bodies)
  - Academia (e.g., Bocconi University, Stockholm School of Economics, University of Reims)
  - Industry (e.g., Marivek Healthcare Consulting, MedTech)
  - Physicians (e.g., Italian Cancer Society, Comprehensive Cancer Centre)

Identified individuals will be invited via email, with a formal letter outlining the project's objectives, their expected roles, participation details, and compensation. The invitations will be managed centrally by a single researcher, who is responsible for contacting potential participants via email while copying research managers on the correspondence to ensure proper oversight.

In addition, participants will be allowed to **suggest additional potential members** for the panel. These suggestions will be reviewed by the research team to ensure that new panellists met the necessary criteria and helped maintain balance and representation across stakeholder groups.

Participants will be compensated **€500** for completing the study, while steering committee members will receive additional compensation based on their broader scope of involvement.

**Stage 3: Framework Adaptation**

The adaptation process will begin with the **starting framework**, adapted from the IECS Value Assessment Framework (VAF) for in-vitro diagnostics in Latin America (LATAM). This adaptation is based on findings from a systematic literature review (see Stage 1 for details). The framework adaptation process was submitted to the **LSE Ethics Committee** for approval prior to the start of the Delphi process.

Before the official launch, the **web platform** and the initial framework presentation will be **piloted** with researchers from the group who were not directly involved in managing or uploading the process. The pilot serves to ensure the platform functions as intended and that framework and the instructions are clearly understood by participants. Feedback from this internal pilot will help refine both the presentation of the framework and the structure of the online platform before wider stakeholder engagement begins.

The Delphi exercise involves conducting four rounds using Welphi, an online survey platform designed specifically to implement the Delphi method. Welphi creates questionnaires to gather opinions from geographically dispersed participants, ensuring anonymity and promoting consensus through a non-face-to-face format.

Participants who do not complete a Delphi round will be excluded from the following round. For example, participants who fail to complete Round 1 are not invited to Round 2. Calendar invites and reminders are to be sent to participants at the beginning of each round to ensure engagement and timely completion.

**Step 1: Delphi Round 1 - Open-Ended Feedback**

The goal of the first round is to present the IECS-adapted framework to participants and obtain feedback in the context of NGS/CGP diagnostics in Europe.

1. **Background Information Presentation**
   - Participants will be introduced to the background and scope of the project: NGS/CGP technologies:

Current impact and future expectations on the health system. NGS/CGP for diagnostics in Europe: The role and integration of these technologies.

1. **Framework Presentation**
   - Participants will be shown the value framework separated into value criteria, including detailed explanations of each.
2. **Feedback Collection**
   - Instructions for R1 are as follows:

*Please review each of the following value statements and proceed as follows: If you think there are issues with the wording or content of a statement, please provide your feedback using the comment button to the right of the value statement.*

*If you believe that we are missing any aspects of value regarding NGS/CGP technology assessment, please click on the ‘add sub-criteria’ button at the bottom of the page and write your thoughts. Try to explain your suggestion as specifically and objectively as possible.*

*Please keep in mind that the purpose of this framework will be to inform decision makers at the time of making coverage, reimbursement or funding decisions.*

- - Participants will be invited to provide comments, suggest additional criteria, and adjust value criteria and sub-criteria where necessary.
  - For each new sub-criteria proposed, participants will be asked to provide an explanation, assign it to an existing value criterion, or suggest a new criteria.

1. **Context-Specific Feedback**
   - Open-ended questions will be posed about NGS/CGP for oncology and rare diseases, asking whether certain sub-criteria were relevant only to these diagnostic contexts.
   - Instructions and the questionnaire for the open-ended section of R1 are as follows:

*Open Page*

- *In your opinion, how should these criteria be grouped?*
- *Write at least three criteria in which the criteria can be grouped.*
- *For example, one criteria could be “clinical characteristics”.*

1. **Round Duration**
   - This round of the Delphi process will remain open for 10-14 days to allow sufficient time for participants to contribute.

**Step 2: Thematic Analysis**

The purpose of this step is to systematically review the feedback received and present a revised framework incorporating participant views.

1. **Data Importation**
   - All comments and proposed criteria from the participants will be imported into Microsoft Excel for analysis.
2. **Coding and Analysis**
   - The data will be coded by theme and value criteria, ensuring all comments are categorized appropriately. This process will be carried out by three researchers, with two researchers reviewing and coding each case. Any disagreements will be resolved by the third researcher, who acted as an arbitrator to ensure consistency and accuracy in the analysis.
3. **Incorporation of Feedback**
   - **Meetings will be conducted** to extensively review participant comments and feedback from Round 1. During these sessions, participant feedback will be incorporated into the appropriate sub-criteria. Duplicates or previously addressed proposals will be removed during the review process, and newly proposed sub-criteria will be reviewed by theme. Where necessary, sub-criteria will be merged or reworded for clarity and consistency to ensure a well-organized and coherent framework.
4. **Revised Framework**
   - A final list of value sub-criteria, including revised, new, and unchanged elements, will be produced and organized by value criteria.
   - A side-by-side comparison of the initilly presented framework and the revised framework will be conducted to highlight the changes.
5. **Timeframe**
   - This stage will be completed over approximately in one month.

**Step 3: Delphi Round 2 - First Value Judgements**

This round aims to collect participants' value judgements on the importance of each value criteria and value sub-criteria for assessing the value of NGS/CGP diagnostics in Europe.

1. **Value Judgement Process**
   - Participants first will rate each **value criteria** on a **Likert scale** ranging from 1 to 5, where 1 represented "not at all important," 2 "low importance," 3 "moderate importance," 4 "important," and 5 "very important." Following this, value sub-criteria will be presented in **separate sections** corresponding to each value criteria on the web platform, and participants will then be asked to assess each sub-criteria using the same scale.
   - Instruction for this round are as follows:

Value Criteria:

*REQUIRED: Independently score the importance level of each criteria on an ‘importance’ Likert scale, ranging from ‘1: Not at all important’ to ‘5: Very important’.*

*OPTIONAL: You may provide a comment if any aspects are unclear. Please note comments will be used for research context only and will not be used to change sub-criteria for the next round.*

Value subcriteria:

*REQUIRED: Please review each of the following value statements in 8 criteria (Clinical impact; Test performance and quality; Quality of scientific evidence; Non-clinical impact; Impact on health system integration; organisation; and delivery of care; Economic aspects; Ethical, legal and data governance aspects; and Health system priorities) according to their importance within a framework for assessing NGS/CGP technologies for oncology. Please score each statement according to a 5-point importance Likert scale, ranging from ‘1: not at all important’ to ‘5: very important’. Please keep in mind that the purpose of this framework is to act as a decision aid for reimbursement and coverage decisions.*

*OPTIONAL: Please comment on the associated sub-criteria if its wording and/or concepts are unclear. Note: comments will be used for research purposes only and will not impact changes in the framework for the next round.*

1. **Mandatory Judgements**
   - Participants will be required to provide a value judgement for each value criteria and sub-criteria.
2. **Round Duration**
   - This stage of the Delphi process will be kept open for 10-14 days.

**Step 4: Delphi Round 3 - Second Value Judgements**

The purpose of this round is to provide participants with the opportunity to revise their previous responses after seeing the collective feedback from Round 2.

1. **Presentation of Results**
   - Participants will be shown the dispersion of responses for each value criteria and value sub-criteria from Round 2, along with their own prior responses.
2. **Opportunity to Revise**
   - Based on this information, participants will be allowed to revise their previous ratings or leave them unchanged.
   - The directions for this section will be similar to those provided in Round 2, with slight adjustments where necessary.
3. **Round Duration**
   - This stage of the Delphi process will remain open for 10-14 days.

**Step 5: Delphi Round 4 - Final Value Judgements**

The purpose of the final round is to stabilize the participants’ judgements, allowing for confirmation and validation of their responses, leading to more robust results.

1. **Validation Process**
   - Similar to Round 3, participants will be shown the distribution of responses and their previous answers. They will be asked to confirm or revise their ratings for each value criteria and sub-criteria.
   - The directions for this section will be similar to those provided in Round 2, with slight adjustments where necessary.
2. **Final Stability**
   - This final round aims to establish greater stability in the results, ensuring that the findings reflected the consensus reached through multiple stages of feedback.

**Stage 4: Statistical Analysis Using Stata**

The objective of this stage is to evaluate the level of agreement across stakeholder groups regarding the importance of NGS/CGP diagnostics in Europe. A series of statistical tests will be applied to analyze participant consistency, agreement, and to identify any significant disagreements between groups. The analyses to be conducted include:

1. **Interrater Agreement (IRA)**: The **Kappa statistic** and **Gwet’s Agreement Coefficient** is employed to measure the extent to which individuals within each stakeholder and country group independently made similar judgments. These metrics assess internal agreement within groups, and groups demonstrating a high degree of internal consistency were compared against one another.
2. **Wilcoxon Test**: This test is used to evaluate the stability of responses within stakeholder groups across Delphi rounds. When significant instability is detected for certain sub-criteria, additional Delphi rounds are considered to achieve consensus.
3. **Interquartile Range (IQR)**: The IQR of the medians is calculated to determine the level of agreement across stakeholder groups. This metric highlights consensus or divergence regarding the importance of specific sub-criteria.
4. **Kruskal-Wallis H Test**: This non-parametric test is used for subgroup analysis to determine whether there are significant disagreements between stakeholder groups on each sub-criteria. Where significant differences are found, **Dunn’s test** is conducted to identify which specific groups disagreed.

Statistical tests will be completed using **STATA 16.1 software** to assess consensus, stability, and median responses across the cohort. Consensus will be evaluated using the **Interquartile Range (IQR)**, with consensus defined as an IQR ≤ 1. The **Wilcoxon test** will be applied to assess the stability of responses between rounds 2 and 3, and between rounds 3 and 4, to determine whether participants changed their opinions over time.

The **inclusion criteria** for the final framework considers both the IQR (≤ 1) and the median response for each sub-criteria. Sub-criteria with a median of "important" or "very important" are classified as **essential** for value assessment, while those with a median of "moderately important" or lower are classified as **complementary** to the assessment process.

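### The Wilcoxon test has little ability to flag instability in stakeholder groups of about five, and at any sample size it misses offsetting changes, so a non-significant result does not show stability

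*Protocol*

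**What the plan says.** Stage 4, item 2 of the Protocol names the Wilcoxon test and its unit: "This test is used to evaluate the stability of responses within stakeholder groups across Delphi rounds". It attaches a consequence: "When significant instability is detected for certain sub-criteria, additional Delphi rounds are considered to achieve consensus". The closing paragraphs of Stage 4 come back to the test. They describe stability as something assessed in the cohort as a whole, and they apply the test between Rounds 2 and 3 and between Rounds 3 and 4, "to determine whether participants changed their opinions over time".

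The group sizes follow from Stage 2. The collaborative stakeholder group "will be formed by a minimum of 30 participants from European countries". "Participants will be divided into six subgroups based on their roles within the healthcare system", and "Similar numbers of participants will be recruited from each group to ensure balanced representation". Stage 3 adds that "Participants who do not complete a Delphi round will be excluded from the following round".

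On the number of rounds, Stage 3 says: "The Delphi exercise involves conducting four rounds using Welphi". Step 5 of that stage calls Round 4 the final round and gives its purpose as stabilising the judgements. Stage 4 sets a numerical threshold for consensus (IQR of at most 1) but none for stability.

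**The concern.** Three things do not fit together.

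- **Sample size.** Tested inside each stakeholder group, the comparison rests on about five pairs at the planned minimum, and on fewer once non-completers are excluded. A test that small will rarely be significant, whatever the participants do.
- **Question asked.** The stated aim is to learn whether participants changed their opinions. A signed-rank test asks whether ratings moved, on balance, in one direction. Rounds 3 and 4 show each participant the distribution of responses beside their own earlier answer. That can draw low raters up and high raters down at the same time, and such moves cancel in the test statistic.
- **Decision rule.** Only a significant result has a consequence, and no positive criterion for stability is given. The natural use of a non-significant result would be to report the item as stable, which small numbers or cancelling moves can produce by themselves.

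At stake are the claim of stability, which is the purpose of Round 4, and the only stated trigger for further rounds.

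**Working it through.** The Protocol gives no power calculation or other figure for this test, so there is nothing to reproduce.

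**Inputs from the Protocol.** Minimum panel 30; six groups of similar size; 5-point scale; comparisons of Rounds 2-3 and 3-4.

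**Assumptions.** The test is the paired signed-rank form, since the same people rate twice. Significance is two-sided at 0.05. Exact and normal-approximation p-values are both shown. Moves are of one point.

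**1. Group size.** 30 / 6 = 5 at the minimum. If the nine listed steering committee members also rate and are spread over the groups (an assumption), (30 + 9) / 6 = 6.5.

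**2. Smallest exact p.** With m non-zero differences, all in one direction, p = 2 / 2^m.

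| m | smallest two-sided p |
|---|---|
| 3 | 0.25 |
| 4 | 0.125 |
| 5 | 0.0625 |
| 6 | 0.031 |

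Unchanged ratings do not count towards m. A group of six with one unchanged rating is therefore back at 0.0625.

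**3. Normal approximation, group of five.** With u moves up and d down, z = (u − d) / √(u + d).

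- five up: z = 5/√5 = 2.24, p = 0.025
- four up, one unchanged: z = 4/√4 = 2.00, p = 0.046
- three up, two unchanged: z = 3/√3 = 1.73, p = 0.083
- four up, one down: z = 3/√5 = 1.34, p = 0.18

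**4. Probability of a significant result**, by enumerating all combinations of up, down and unchanged:

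| n | 60% up, 10% down: exact / approx. | 80% up, 0% down: exact / approx. |
|---|---|---|
| 5 | 0 / 0.27 | 0 / 0.74 |
| 6 | 0.05 / 0.36 | 0.26 / 0.90 |
| 30 | 0.93 / 0.96 | 1.00 / 1.00 |

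**5. Offsetting changes in a panel of 30.** Ten up, ten down, ten unchanged: z = (10 − 10) / √20 = 0, p = 1.0, while 20/30 = 67% changed. If each participant has a 40% chance of moving up and 40% of moving down, so that 80% change on average, the probability of significance is 0.03 exact or 0.05 approximate. That is no better than chance.

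**6. The opposite error.** Six of 30 move up and none down: exact p = 2/2^6 = 0.031, which is significant although 24/30 = 80% of ratings are unchanged.

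**7. Text set side by side.** Item 2 of Stage 4 puts the test within stakeholder groups, while the later paragraph puts stability at cohort level. By step 4, the choice decides whether a net shift can be seen. Stage 3 plans four rounds with Round 4 final, while item 2 allows more rounds to be considered. It does so to achieve consensus, although the trigger is instability, which is a different property.

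**The case against.** The strongest reply is that the cohort-level wording is the operative one. At n = 30 a net shift is readily detected (0.93 in the first scenario), and the small-group argument falls away. Moreover, 30 is a floor, and steering committee members may add to it. The Protocol fixes no significance level, sidedness or exact method. Such details may sit in an analysis plan not shown here, and their absence is no fault. By normal approximation, four or five of five moving together does reach significance.

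All of this stands as a limit on the sample-size argument. A reader might infer that no stakeholder group could ever be flagged, or that stability would be declared automatically. The documents do not support that: it needs groups of five or fewer and an exact two-sided 0.05 test, and the Protocol fixes neither. Nor does it state that a non-significant item will be called stable. It says only what follows when instability is significant.

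A second reply is that convergence is what controlled feedback is meant to produce, and that the IQR would show it. That is partly right. But the IQR describes the distribution, not individual change: if ten participants move from 3 to 4, ten from 4 to 3 and ten stay, the distribution, IQR and median are all identical while 67% have changed. The blindness to offsetting moves therefore survives at cohort level.

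Finally, further rounds are only to be considered, so the conflict with four planned rounds is a tension in wording and not a flat contradiction.

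**Conclusion.** The point holds in this form. At the planned minimum, a within-group signed-rank test has little ability to flag instability, and none if it is exact and two-sided at 0.05 (smallest p 0.0625). By normal approximation, which is unreliable at n = 5, at least four of five must move together with none opposing. These figures rest on groups of about five; exclusion of non-completers can make them smaller, but no attrition rate is given.

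Independently of group size and of how p is computed, the test detects only net shift. It cannot establish whether participants changed their opinions, and non-significance should not be read as stability.

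A reader might also infer that sub-criteria could be wrongly included or classified as a result. The documents do not support that: inclusion and the essential or complementary label depend on the IQR and median, and stability gates neither. The damage is limited to the stability claim and to the decision about further rounds.

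**What to change.** In Stage 4:

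- State one unit for the stability assessment, so that item 2 and the closing paragraphs agree. The whole panel, restricted to paired completers, is the workable choice.
- Define stability per sub-criterion as the percentage of ratings unchanged between Rounds 2 and 3 and between Rounds 3 and 4, against a threshold chosen by the team before Round 3 opens. The documents give no basis for a particular value.
- Support it with a weighted between-round agreement coefficient.
- Keep the Wilcoxon test only as a whole-panel description of net shift, and say that a non-significant result is not evidence of stability.
- Reconcile the sentence on additional rounds with the four planned rounds and with Round 4 as the final one, and separate instability from lack of consensus. Deleting the sentence is one option, not a necessity.

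The cost is some rewording and a small tabulation. The ratings are mandatory and already collected in each round, so no new data are needed. The downside is that some items may have to be reported as unstable.

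### The only IQR that Stage 4 defines is that of the six group medians; if the ≤ 1 consensus and inclusion rule uses it, items with widely spread ratings can pass as agreed

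*Protocol*

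**What the plan says.** All the rules are in the protocol, Stage 4 (Statistical Analysis Using Stata).

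- Item 3 introduces the agreement metric: "The IQR of the medians is calculated to determine the level of agreement across stakeholder groups". It carries no cut-off. It adds that the metric shows where there is consensus or divergence on a sub-criterion.
- The paragraph after the numbered list says the tests serve "to assess consensus, stability, and median responses across the cohort", and that consensus is judged by the IQR, "with consensus defined as an IQR ≤ 1". It does not say what the IQR is taken over.
- The last paragraph says inclusion in the final framework "considers both the IQR (≤ 1) and the median response for each sub-criteria". The median then sorts sub-criteria into essential (important or very important) and complementary (moderate or lower).
- Item 1 plans kappa and Gwet's coefficient for agreement within groups. Item 4 plans Kruskal-Wallis with Dunn's test for disagreement between groups. Neither is mentioned in the consensus or inclusion rule.

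The panel is described under Stage 2: "Participants will be divided into six subgroups based on their roles within the healthcare system", it "will be formed by a minimum of 30 participants from European countries", and "Similar numbers of participants will be recruited from each group to ensure balanced representation". Ratings are given "on a Likert scale ranging from 1 to 5" (Step 3, Delphi Round 2).

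**The concern.** A cut-off of 1 on a five-point scale is informative when the IQR is taken over individual ratings: the middle half of the panel then lies within one category. Taken over six group medians, the same cut-off means something else. Each median has already discarded the spread within its group, and the quartiles of only six values say little about the two outermost groups.

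The IQR decides whether a sub-criterion counts as agreed and, with the median, how it enters the framework. The framework is meant to support coverage and reimbursement decisions, and the stated aim of Stage 4 is to evaluate agreement across stakeholder groups. If the rule is run on the medians, items can be reported as consensus when panellists are far apart. If the text is simply open, two rules with very different pass rates are available, and the choice could be made after the ratings are seen.

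**Working it through.** **Inputs from the protocol.** Six groups; at least 30 panellists in similar numbers per group, so 30/6 = 5 per group at the minimum; scale 1 to 5; cut-off IQR ≤ 1. The protocol gives no expected pass rate or error rate for the rule, so there is no figure to reproduce.

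**Assumptions not in the protocol.** Equal groups of 5 to 10, the rating distributions named below, and the quartile definition. The protocol names Stata 16.1, so its default is the main case. Linear interpolation (type 7) and the (n+1)p definition were also run.

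**1. Spread within groups.** Let every group of five rate 1, 2, 3, 4, 5.
- Group medians: 3, 3, 3, 3, 3, 3. IQR = 3 − 3 = 0: pass.
- Individual ratings: six of each value, n = 30. Stata's Q1 is the 8th ordered value (2) and Q3 the 23rd (4). IQR = 4 − 2 = 2: fail.

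**2. Pass rates under uniform random ratings (20% on each category), 100,000 simulated panels.**

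| Per group | Medians, Stata default | Individual, Stata default | Medians, (n+1)p | Individual, (n+1)p |
|---|---|---|---|---|
| 5 | 64% | 3.8% | 19% | 0.9% |
| 6 | 63% | 1.4% | 27% | 1.4% |
| 7 | 74% | 1.9% | 28% | 0.5% |
| 10 | 76% | 0.4% | 42% | 0.4% |

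Type 7 gave the same values as the Stata default here.

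**3. Other distributions, five per group, Stata default.**
- Broad (10/15/25/30/20% on 1 to 5): 88% pass on medians, 36% on individual ratings.
- Polarised (half at 1, half at 5): 22% against 0.5%.

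**4. Pass and pooled median of at least 4 (essential), uniform, five per group, Stata default.** 6.7% on medians, 0.66% on individual ratings. Most spurious passes under uniform ratings would therefore be complementary items.

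**5. One dissenting group.** With six values, Stata's quartiles are the 2nd and 5th in order.
- Medians 1, 5, 5, 5, 5, 5: IQR = 5 − 5 = 0. With (n+1)p, Q1 = 0.25 × 1 + 0.75 × 5 = 4, so IQR = 5 − 4 = 1. Both pass.
- Individual ratings, five 1s and twenty-five 5s: the dissenters are 5/30 = 16.7%, below the 25% point, so IQR = 0. This also passes.
- Medians 1, 1, 5, 5, 5, 5: IQR is 3 to 4 depending on the definition. Two dissenting groups fail the rule.

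**6. What Kruskal-Wallis would show.** For five groups all at 5 and one all at 1 (five raters each), H = 29 and p = 0.00002. For an assumed moderate dissent (five groups at 0/5/15/40/40%, one at 15/30/30/20/5%), power at the 5% level is about 40%.

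**The case against.** **The cut-off may already be meant for individual ratings.** Item 3 carries no threshold. The threshold appears in a paragraph about the whole cohort, and the inclusion rule pairs it with one median per sub-criterion, not six. A reader might infer that the protocol expressly applies ≤ 1 to the group medians. It does not, and this objection stands as far as it goes. But the IQR of the medians is the only one defined, and nothing signals a switch, so it remains the natural reading. If individual ratings are intended, the text still needs to say so.

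**The simulation has no between-group disagreement.** All groups are drawn from one distribution, so a small IQR of medians correctly answers whether groups differ. This is fair: the statistic fails as a test of panel consensus, not as a rough description of group differences. The rates also depend on assumed ratings, and uniform answers after rounds of feedback are an unfavourable case. The claim is that items *can* pass without agreement, not that they always do.

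**Blindness to one group is not special to medians.** Correct: with six equal groups the pooled IQR shares it (step 5), so moving the cut-off does not cure it.

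**The plan has other checks.** A reader might infer that dissent would go unseen. The documents do not support that: kappa/Gwet and Kruskal-Wallis/Dunn are planned, and the extreme case would be flagged. What remains is that these results change neither the consensus label nor inclusion.

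**Conclusion.** The point holds in a bounded form. Stage 4 defines one IQR, over six medians, and rests consensus and inclusion on IQR ≤ 1 without naming another. On that reading the rule discards within-group disagreement. With six groups of five and uniform ratings, the pass rate is 64% rather than 3.8% (Stata default), or 19% rather than 0.9% ((n+1)p). The medians rule was the more lenient one for every distribution, group size and quartile definition run; the size of the gap rests on those assumptions. Separately, neither IQR detects one dissenting group in six, and the analyses that might do so have no bearing on the rule. An express instruction to apply the cut-off to the medians, or an absence of any check on group disagreement, would be a stronger finding than the text supports.

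**What to change.** Amend Stage 4 before the final ratings are analysed.

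1. State that consensus (IQR ≤ 1) and the median for each sub-criterion are computed on the individual final-round ratings of all panellists.
2. Keep the six group medians as description. Report all six, with minimum and maximum, in place of their IQR.
3. Label any included sub-criterion with a significant Kruskal-Wallis result as 'panel consensus, group divergence', naming the groups identified by Dunn's test, and do not claim agreement across stakeholder groups for it.

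Requiring the range of the six medians to be ≤ 1 is a tempting alternative to the third step, but it is too noisy. With medians of five raters and all groups sharing one distribution, it would label about 38% (broad distribution) or 19% (an assumed converged distribution, 2/5/18/45/30%) of pooled-consensus items divergent by chance.

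The cost is a few sentences, with no new data and no new tests. Fewer sub-criteria will meet consensus. Kruskal-Wallis will miss much moderate dissent at about five raters per group (power about 40% in the case above), so a non-significant result should not be reported as proof that the groups agree.
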